#### Sample size

The power estimation was based on an assumption of independence in the data (see Table 4, line A). The power was then adjusted on the need for a multi-level approach, as cases will be clustered in schools (see Table 4, line B) [32, 33]. The desired significance level is *p* = 0.05 and power is 0.80. The following additional conditions were accounted for: (1) anticipated effect size (*d*) of the main factors: 0.25 (conservative estimate), (2) the intraclass correlation coefficient (ICC): 0.05 (estimate is based on the level of school affiliation in Norway) [34], (2) average size of the clusters = 20 (i.e.: number of individuals within each school in a 24-month intervention period). Ukoumunne and colleagues’ equations ([33]; page 31 and 32) and Altman’s recommendations are used [35].

The total of individuals should be at least N = 796 across 40 schools. With eight experimental conditions, 5 schools will be assigned to each condition. With 40 schools, 20 children per school will be needed (see Table 4, line B).

**Table 4 Tab4:** Number of participants and clusters required in a multilevel study

	Assumed ICC	Design effect	*N* indiv	*n/*cluster	*N schools*
A	0.00 – Base model	1	400	20	20
B	0.05 – Two-level model	1.95	800	20	40

Design effect = 1 + (n_c_ − 1)

*ICC* intraclass correlation coefficient, *n* number of pupils

*ICC (n_c_ = average number of individuals in a cluster = 20)

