School eligibility will be determined by region of the country and municipality. School-size is a recruitment criterion, as the participating schools need to have at least one full class in each grade to increase the probability of recruiting enough children to run an EMOTION group. The study will be presented to key personnel (principals at schools, heads of different primary care health agencies) at each site. The person responsible for each site or health agency will sign a statement of intention to participate in the study, while interested schools will also sign an agreement to participate in the study and are asked to nominate a contact person. The intervention will be offered each semester (autumn/spring term) of each school year. The plan is to include an average of five children from each grade in each school every semester, but group size may vary with between three and seven children per group. The children are screened prior to participation (T1) and assessed after the intervention (T2) (see Table 2). One year after the end of the intervention, the children will complete the same self-report measures to identify possible long-term effects (T3), an important goal for all preventive interventions. Responsibilities of school contacts include informing teachers and parents at the targeted grades about the study and facilitating the completion of the child surveys at the measurement times (T1-T3). Children are presented with age-appropriate oral and written information about the study. Parents are informed about the study during parental meetings and receive a link to detailed written information and electronic consent. Parents are invited to consent on the child`s behalf if they consider that their child has more sad or anxious feelings than peers and the child wishes to participate in a group. Both parents (or one parent with single parent care) must provide a consent before a child can participate. Presentations and videoclips are available to help recruit schools and children. The recruitment of participants is reported in accordance with the Consolidated Standards of Reporting Trials (CONSORT) guidelines for clustered randomized trials [20]. A project webpage (https://www.echo.r-bup.no) is developed to enhance the communication between all participants.

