#### Primary outcomes

The primary outcomes of interest for this study are changes in level of depression and anxiety from pre- to post-intervention and from pre-intervention to follow-up. The null hypotheses for the primary outcomes of this study are that there will be no differences in changes of depression or anxiety scores between the three factors (main effects). The primary outcome measures will be based on two informants: children and parents.

Depression is assessed using the SMFQ [21], a 13-item measure assessing cognitive, affective, and behavioral-related symptoms of depression in children 8–18 years. Anxiety is assessed using the MASC-C/P [23], a 39-items self-report measure for adolescents between 8 and 19 years. Parents will use the parent version of the same instruments.

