### Planned statistical analysis

Several models will be run to test for the main treatment outcomes, implementation outcomes, and related research questions.

The analyses will involve changes in outcome variables. A combination of linear mixed models and latent growth curve analyses will be used to identify differences between treatment groups, as well as change rates in growth over time. Based on the experience from the previous study, the rate of missing data due to electronic data collection will be low. Otherwise, missing data will be accounted for using full information maximum likelihood in growth curve analyses and restricted maximum likelihood techniques in mixed effects models where applicable, well-established techniques that allow for the inclusion of all available data.

To investigate the psychometric properties of some instruments initial exploratory factor analyses will be performed to investigate which factors we are able to obtain from our sample. Further, confirmatory factor analysis will be used. Correlations between subscales will be computed using Pearson’s r. Internal consistency for the subscales will be measured with Cronbach’s alpha.

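### The stated 0.80 power assumes complete outcomes from every required child; no attrition is allowed for, although one-year change is primary

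*Protocol article*

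**What the plan says.** All references are to the protocol article; no separate statistical analysis plan is at hand.

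- **Sample size.** The significance level and target power are given as "0.05 and power is 0.80". The anticipated effect is "of the main factors: 0.25 (conservative estimate"), and clustering enters as "the intraclass correlation coefficient (ICC): 0.05" with an average of 20 children per school. The 20 is explained as a school's participants over 24 months of intervention. The conclusions are "The total of individuals should be at least N = 796 across 40 schools" and "With 40 schools, 20 children per school will be needed". Table 4 gives 400 children before and 800 after a design effect of 1.95. Attrition is not among the listed conditions.
- **Primary outcomes.** Change to post-intervention (T2) and change to one-year follow-up (T3) are both primary, each by child and parent report. The null hypotheses are "that there will be no differences in changes of depression or anxiety scores between the three factors (main effects").
- **Planned statistical analysis.** Citing the previous study, the article expects that "the rate of missing data due to electronic data collection will be low". It gives no rate. Available data enter through full information or restricted maximum likelihood.
- **Recruitment and eligibility criteria; Randomization.** The planned intake averages five children per grade, per school, per semester, and "group size may vary with between three and seven children per group". Each school stays for about five semesters.

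**The concern.** The same 20 per school serves as the number taking part and as the number analysed. That holds only if every child and every parent supplies the primary outcomes, including those due a year after the groups end. A child may leave a group or change school, and a parent may not answer an emailed or texted link. Electronic collection does not by itself prevent either.

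At stake is the trial's claim about what it can detect at T3, and from parents at either time point. If a main effect is not significant there, a reader will judge that result against a power of 0.80 that the section does not establish for those data.

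**Working it through.** **Inputs.** d = 0.25 (SD 1), alpha 0.05, power 0.80, ICC 0.05, 40 schools and 20 per school, all from the sample-size section. With eight conditions of five schools, each main effect compares 20 schools with 20. Loss rates of 10% and 20% are assumptions, since the article gives none.

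**Step 1: reproduce the plan.** n per arm = 2(z_alpha + z_power)² / d².

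- One-sided: 2(1.645 + 0.842)² / 0.0625 gives 198 per arm, 396 in all. A t-based calculation gives 199 and 398. Then 396 × 1.95 = 772, 398 × 1.95 = 776, and 398 × 2 = 796 exactly.
- Two-sided: 2(1.960 + 0.842)² / 0.0625 gives 252 per arm, 504 in all, and 504 × 1.95 = 983.

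The design effect is 1 + 19 × 0.05 = 1.95, as in Table 4. So 400 and 796 fit d = 0.25 only with a one-sided test. Two-sided, a base of 400 corresponds to d of about 0.28.

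**Step 2: power after loss.** With m analysed children per school, DEFF = 1 + (m − 1) × 0.05, effective N = 40m / DEFF, and power = Φ(0.25 × √(effective N) / 2 − z_alpha).

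| Loss | Analysed | m | DEFF | Effective N | One-sided | Two-sided |
|---|---|---|---|---|---|---|
| 0% | 800 | 20 | 1.95 | 410 | 0.812 | 0.716 |
| 10% | 720 | 18 | 1.85 | 389 | 0.794 | 0.694 |
| 20% | 640 | 16 | 1.75 | 366 | 0.772 | 0.667 |

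**Step 3: where 0.80 is crossed (one-sided).**

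- Design effect held at 1.95: about 772 children, so 800 − 772 = 28 losses (3.5%).
- School sizes shrinking with loss: about 744 children, so 800 − 744 = 56 losses (7%).
- At 796, power is still 0.812.
- Two-sided, 0.80 is not reached even at 800.

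**Step 4: sensitivity to the approximation.** A t reference with 36 degrees of freedom lowers the figures by 1 to 2.5 points. At 800 with no loss it gives 0.799 one-sided and 0.693 two-sided.

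**Step 5: intake against requirement.** Even at only five children per school per semester, five semesters give 5 × 5 = 25 per school, and 25 × 40 = 1000. A 20% loss would leave 800 and return the first row of the table. Table 2 (footnote b) allows schools to join later, which would lower this intake.

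**The case against.** The best defence has three parts.

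**Intake may exceed 800.** The 796 and 800 are stated as requirements, not as an enrolment target or ceiling, and the described recruitment could yield about 1000. This stands, and it may turn out to cover the loss. But the sample-size section does not mention a surplus or present one as the allowance for attrition.

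**Missing data are addressed.** The low expected rate is attributed to earlier experience, the retention section provides reminders and school contact, and likelihood methods use all available data. This stands in part. The table above drops lost children altogether and so gives no credit for their earlier measurements; the gain cannot be computed, because the article gives no correlation over time. Likelihood methods still do not restore all the lost information.

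**Unequal schools may matter little.** The article speaks of an average of 20, and the range of three to seven applies to groups, not schools. If group sizes were spread evenly over that range (an assumption), a school total over four groups would have a coefficient of variation (CV) of about 0.14, and one-sided power would move only from 0.812 to 0.809. Staggered entry could add more. Nothing in the article supports a value as high as 0.5.

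A reader might also infer from 800 against 796 that the plan can afford to lose only four children. The calculation does not support that. Four is the effect of rounding to whole schools of 20, and losing four changes power by about 0.001.

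**Conclusion.** The point holds in a limited form. The stated 0.80 is a complete-data figure for 800 children, while two of the primary comparisons are of change to one year, by child and by parent report, with no loss rate given. Attrition alone costs about 2 points at 10% loss and 4 points at 20%, bringing one-sided power to 0.79 and 0.77.

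Unstated sidedness costs more: a two-sided test puts power at 0.72 before any loss, then 0.69 and 0.67. The article does not say which test was intended. That the calculation was one-sided is inferred from its figures, and that the test should be two-sided is inferred from the wording of the null hypotheses.

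These values assume 800 enrolled, equal schools, a normal approximation, and no information recovered from children with partial data. They do not show that the trial will fall short: if intake exceeds 800 by enough, the analysed number may still reach the requirement. What is unsupported is the power statement as written.

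**What to change.** Keep enrolment as planned and revise the sample-size section:

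- State whether the test is one- or two-sided, and recompute on that basis.
- Give power separately for T2 and T3, and for child and parent report, using analysed children per school after an expected loss taken from the group's earlier 36-school trial. The article does not report that retention, so the authors must supply it.
- Replace the design effect by 1 + ((1 + CV²) × m − 1) × ICC, with m the mean analysed children per school and CV the observed coefficient of variation of school size.
- Say whether the five-semester intake is the intended buffer and, if so, how many children it is expected to add.

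The sentence on low missing data in the planned statistical analysis can stay, since it cites experience that the article does not show. It should carry a rate, and it should not serve in place of an attrition allowance.

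The cost is a short recalculation and rewording. If intake stays at 800, the stated power becomes less favourable: at 10% to 20% loss, 0.79 to 0.77 one-sided or 0.69 to 0.67 two-sided.

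### The stated 0.80 power for d = 0.25 matches a one-sided 5% test; for the undirected null hypotheses, an unadjusted two-sided test with 40 schools of 20 has about 70%

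*Protocol article*

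**What the plan says.** The Sample size section of the protocol article fixes the error rates in one sentence: "The desired significance level is *p* = 0.05 and power is 0.80". Sidedness is not mentioned there or elsewhere in the article. The other inputs are an anticipated effect of d = 0.25 for each main factor, described as conservative, "the intraclass correlation coefficient (ICC): 0.05", and "average size of the clusters = 20".

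Table 4 turns these into two lines. Line A assumes independence and gives 400 children. Line B applies a design effect of 1.95 and gives 800 children in 40 schools. The text sets a minimum of 796 and concludes: "With 40 schools, 20 children per school will be needed". Five schools go to each of the eight conditions, so each main effect compares 20 schools with 20.

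The Primary outcomes section gives the hypotheses: "The null hypotheses for the primary outcomes of this study are that there will be no differences in changes of depression or anxiety scores", applied to the three main effects. No direction is attached to any factor.

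**The concern.** A null of no difference with no stated direction is ordinarily tested two-sided. The Background gives no reason to read the factors as one-directional. The partly digital version replaces half of the group sessions and is motivated in part by cost, and earlier findings on parental involvement are described as mixed. For both factors an effect in the unexpected direction is possible, and a one-sided test could not declare it.

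If the calculation is one-sided and the tests are two-sided, the stated power is too high. The trial is meant to show which components are worth keeping. A null result for the digital format, the feedback system or the parent groups would be read as though the chance of missing d = 0.25 were 20%, when it would be nearer 30%.

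**Working it through.** **Inputs**, all from the Sample size section and Table 4: d = 0.25, significance level 0.05, power 0.80, ICC 0.05, 20 children per school, 40 schools, equal allocation for each main effect. Standard normal quantiles: 0.8416 for 80% power; 1.645 for one-sided 5%; 1.960 for two-sided 5%.

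**Design effect.** 1 + (20 − 1) × 0.05 = 1.95, as in Table 4 line B.

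**Line A (independence).** Total N = 4 × (z_α + z_power)² / d².
- One-sided: 4 × (1.645 + 0.8416)² / 0.0625 = 395.7. This is 198 per level, 396 in total, or 398 by the t-test. The printed 400 is reproduced.
- Two-sided: 4 × (1.960 + 0.8416)² / 0.0625 = 502.3. This is 252 per level, 504 in total, or 506 by the t-test. The printed 400 is not reproduced.

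**Power at line A as printed.** The noncentrality is 0.25 × √400 / 2 = 2.50.
- One-sided: Φ(2.50 − 1.645) = 0.804.
- Two-sided: Φ(2.50 − 1.960) = 0.705.

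The gap is therefore present before clustering enters and does not depend on the design effect.

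**Power of the planned design.** The effective N is 800 / 1.95 = 410.3, and the noncentrality is 0.25 × √410.3 / 2 = 2.532. The t figures use school-level degrees of freedom: 38 (40 − 2), 36 (40 − 4) and 32 (40 − 8).

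| Test, 40 × 20, d = 0.25 | Normal | t, 38 df | t, 36 df | t, 32 df |
|---|---|---|---|---|
| One-sided 5% | 0.812 | 0.800 | 0.799 | 0.798 |
| Two-sided 5% | 0.716 | 0.694 | 0.693 | 0.690 |

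At the stated minimum of 796 the two-sided figures are 0.714 (normal) and 0.688 to 0.692 (t).

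**Effect detectable with 80% two-sided power at 40 × 20.** (1.960 + 0.8416) × 2 / √410.3 = 0.277, or about 0.28 (normal approximation).

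**Effect of baseline adjustment.** The article gives no pre-post correlation, so r here is an assumption. If d is on the raw-score scale and the analysis adjusts for baseline, N scales by 1 − r². The two-sided total under independence becomes 502.3 × (1 − 0.16) = 422 at r = 0.4, and 502.3 × (1 − 0.25) = 377 at r = 0.5.

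**The case against.** The strongest reply is that sidedness is not stated and that the method rests on cited equations and recommendations not at hand. That is correct, and it limits the claim. A reader might infer that the trial has adopted a one-sided test. The article does not say so; the one-sided reading comes only from the arithmetic. It is tempting to add that 398 × 2 equals 796 exactly, but this replaces the printed design effect of 1.95 by 2, a rounding the article does not mention, so it is weak support. What stands is narrower: the printed inputs do not give 400 for an unadjusted two-sided test.

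The second reply is that the outcome is change from baseline, analysed by mixed and growth models, so real power could exceed that of a simple two-group comparison. This stands too. At an assumed r = 0.45 the two-sided total under independence is 502.3 × (1 − 0.2025) = 401, close to line A. At r = 0.5 with the design effect unchanged, 40 × 20 gives about 0.83 (normal) or 0.81 (t, 36 df). But the Sample size section neither claims such a gain nor gives a correlation, so the printed calculation cannot rest on it. It does mean that 70% must not be presented as the power of every possible analysis.

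Three further inferences are not supported:
- That 796 and 800 conflict. The first is a minimum and the second is 40 × 20; they are compatible.
- That power at one year is lower by a known amount. The Planned statistical analysis section expects little missing data and gives no loss rate, so any figure would be invented.
- That a particular larger trial is required. The two-sided total depends on the method: about 980 children in 49 schools by the normal approximation, 51 to 52 schools with school-level degrees of freedom. The power can be restated without enlarging the trial.

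**Conclusion.** As written, the stated power of 0.80 does not follow from the stated inputs and the undirected hypotheses. For an unadjusted two-sided 5% test, line A should be about 504 (502 to 506 by method), not 400. With 40 schools of 20, ICC 0.05 and equal school sizes, power at d = 0.25 is about 0.72 (normal) or 0.69 (t), a type II error of 28 to 31% in place of 20%. The effect detectable with 80% power moves from 0.25 to about 0.28.

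This rests on two readings: that the undirected nulls call for a two-sided test, and that no variance reduction from baseline is assumed, since none is stated. The shortfall is moderate. Allocation, outcomes and planned models are untouched, and a null main effect can still be judged from its confidence interval.

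**What to change.** In the Sample size section, state that the main-effect tests are two-sided at 5%. Correct Table 4 line A to about 504. Keep 40 schools of 20 in line B, but label it as the planned design and not as the number required for 0.80 power. Restate its power as about 70% for d = 0.25, or 80% for d of about 0.28, without baseline adjustment.

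If the sponsor relies on baseline adjustment, state the assumed pre-post correlation and its source, say on which scale d is defined, and recompute the power. If a one-sided test was intended, say so and reconcile it with the hypotheses in the Primary outcomes section.

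The cost is a change to text and one table. No extra children or schools are asked for; the only downside is a less favourable stated power.

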### Planned statistical analysis

Several models will be run to test for the main treatment outcomes, implementation outcomes, and related research questions.

The analyses will involve changes in outcome variables. A combination of linear mixed models and latent growth curve analyses will be used to identify differences between treatment groups, as well as change rates in growth over time. Based on the experience from the previous study, the rate of missing data due to electronic data collection will be low. Otherwise, missing data will be accounted for using full information maximum likelihood in growth curve analyses and restricted maximum likelihood techniques in mixed effects models where applicable, well-established techniques that allow for the inclusion of all available data.

To investigate the psychometric properties of some instruments initial exploratory factor analyses will be performed to investigate which factors we are able to obtain from our sample. Further, confirmatory factor analysis will be used. Correlations between subscales will be computed using Pearson’s r. Internal consistency for the subscales will be measured with Cronbach’s alpha.

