### Randomization

Participants are randomized at the school-level. The schools are randomized into one of the eight different experimental conditions. Each school agrees on participation for approximately five semesters, entailing five waves of data collection. The school randomization procedure is carried out in the statistical software R, using a function specifically written for the ECHO study by the project statistician in collaboration with key personnel. The actual randomization (running the R function) is witnessed by an objective third party. The function takes two important aspects into account: (1) a balanced distribution of schools to the eight factors, even if the number of schools will be uneven, e.g. in case of new schools, and (2) a balanced distribution of the varying workload caused by the different conditions. The latter is to assure that it is not possible to overload a service provider with assignment of multiple resource demanding intervention conditions.

The randomization procedure was performed in two steps. In the first step, the municipalities were allocated to the two most demanding conditions. These municipalities were randomly drawn proportional to the number of schools within the municipality to ensure that each school had approximately the same probability of being allocated to one of these conditions. After the municipalities were selected, one random school was selected within each municipality. In stage 2, the remaining schools were allocated to the remaining conditions. The function that was used first sorted schools by size, then divided them into size groups equal to the number of remaining conditions. If one of the remaining conditions was allocated to only five schools, one size group was subsequently selected to have this condition reduced. Within the size groups the schools were randomly allocated to the remaining conditions so that the correct number of schools are allocated to each condition.

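### Growth-curve tests of the three factors rest on maximum likelihood with 40 schools; without a small-sample correction a nominal 5% main-effect test rejects about 6–7% of the time, so take the factor tests from the planned REML mixed model

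*Protocol article*

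**What the plan says.** The Randomization section fixes the unit: "Participants are randomized at the school-level". The Sample size section gives the scale: "The total of individuals should be at least N = 796 across 40 schools", with five schools in each of the eight conditions, so each factor compares 20 schools with 20.

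Under Planned statistical analysis, two model families share the comparison of groups: "A combination of linear mixed models and latent growth curve analyses will be used to identify differences between treatment groups". The same section assigns an estimator to each family: "missing data will be accounted for using full information maximum likelihood in growth curve analyses and restricted maximum likelihood techniques in mixed effects models". The Data analysis section places all of this in a multilevel framework at school level.

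Under Primary outcomes, the null hypotheses concern the main effects of the three factors. The Background says that the design permits interactions to be tested, but does not put them in the primary model.

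The article does not say which family gives the factor test, how school enters the growth curve, what reference distribution is used, or whether a small-sample correction applies.

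**The concern.** A school-level factor is tested against variation between schools, and there are only 40 of them. Maximum likelihood makes no allowance for the fixed effects already estimated when it estimates that variation, so it comes out too small. REML makes the allowance. The plan therefore has two analyses of the same factor whose standard errors differ systematically, and no rule for which one counts.

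The trial exists to decide which components to keep. If the two analyses fall on either side of 0.05, the growth curve will tend to give the smaller p-value, for a reason unrelated to the data. A low rate of missing data, which the plan expects, does not help: the bias is present with complete data.

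**Working it through.** **Inputs.** From the Sample size section: 40 schools; "average size of the clusters = 20 (i.e.: number of individuals within each school in a 24-month intervention period"; "the intraclass correlation coefficient (ICC): 0.05 (estimate is based on the level of school affiliation in Norway"; "The desired significance level is *p* = 0.05 and power is 0.80"; "anticipated effect size (*d*) of the main factors: 0.25 (conservative estimate". My assumptions: the test is two-sided at 5%, school is a random effect, and the ICC of 0.05 applies to change scores with total SD 1.

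**The plan's own figure.** The article states no type I error, so its only figure to reproduce is the sample size. The design effect is 1 + (20 − 1) × 0.05 = 1.95, as in Table 4, and 40 × 20 = 800. A one-sided 5% t-test at d = 0.25 and power 0.80 needs 398 children (Table 4: 400). Then 398 × 1.95 = 776 and 398 × 2 = 796. A two-sided test needs 504, or 983 after the design effect. Sidedness there is a separate question. Only 40 schools, 20 children and ICC 0.05 are used below.

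**Set-up.** In a balanced design each school mean has variance V = 0.05 + 0.95/20 = 0.0975. A factor effect is a difference between two averages of 20 school means, with variance V × (1/20 + 1/20) = V/10 = 0.00975 and standard error 0.0987. With p school-level fixed effects, the residual sum of squares has 40 − p degrees of freedom: 36 for intercept plus three main effects, 32 with all interactions. REML divides by 40 − p and maximum likelihood by 40. Let T follow t on 40 − p degrees of freedom under the null.

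**Rejection rules for main effects (p = 4).**
- ML, Wald z: |T| > 1.96 × √(36/40) = 1.859, giving 7.1%.
- ML, likelihood ratio: 40 × ln(1 + T²/36) > 3.84, so |T| > 1.905, giving 6.5%.
- ML, t on 36 df: |T| > 2.028 × √(36/40) = 1.924, giving 6.2%.
- REML, z: |T| > 1.96, giving 5.8%.
- REML, t on 36 df: 5.0%.

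**All interactions in the model (p = 8).** The same rules on 32 df give 8.9%, 8.2% and 7.8% for the three ML tests, 5.9% for REML with z and 5.0% for REML with t.

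**Simulation check.** With 200,000 balanced data sets at ICC 0.05 and the school variance bounded at zero, ML with z rejected 7.2% (p = 4) and 8.9% (p = 8); REML with t rejected 5.0% in both. With unequal school sizes (6,000 runs), ML with z gave 7.0% and 8.9%.

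**Sensitivity to the ICC (ML with z, simulated).**

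| ICC for change | Main effects | All interactions |
|---|---|---|
| 0 | 4.7% | 5.0% |
| 0.01 | 6.0% | 6.7% |
| 0.02 | 6.7% | 7.8% |
| 0.05 | 7.2% | 8.9% |
| 0.10 | 7.0% | 8.8% |

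**Intervals.** For main effects, the REML t interval is √(40/36) × 2.028/1.96 = 1.09 times as wide as the ML z interval. With V at its planning value, the half-width is 2.028 × 0.0987 = 0.20 SD rather than 1.859 × 0.0987 = 0.18 SD. With all interactions the ratio is √(40/32) × 2.037/1.96 = 1.16.

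**The case against.** The strongest reply is that the article names no reference distribution and excludes no small-sample correction, and that a condensed article may leave such detail to the full protocol or analysis plan. That stands against any claim that the growth-curve tests will reject at a particular rate. It does not dispose of the point, because the estimator is named. With the maximum likelihood variance, main-effect tests exceed 5% under all three usual references (6.2–7.1%); the choice of reference changes only the size of the excess.

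Four further objections are sound and limit the point:
- The primary hypotheses are main effects, so a reader who infers 7–9% for every factor test goes too far. The upper part of that range needs all interactions in the same model, which the article does not specify.
- A reader might take the growth curve to be a designated confirmatory model. The text gives neither family that status, and the sentence naming the estimators is about missing data. FIML is a valid way to handle missing data; the weakness is its variance estimate with few clusters.
- The ICC of 0.05 is not said to apply to change, and the check uses a two-level model of change, not the full growth curve over three time points. At an ICC near zero the excess disappears.
- Most of the remedy is already planned, since REML mixed models are one of the two families. What is missing is their priority for the factor tests and a degrees-of-freedom method.

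**Conclusion.** The point holds in a conditional form and is a cheap improvement. If factor effects are tested from the growth curves without a small-sample correction, a nominal 5% test of a main effect rejects about 6–7% of the time at the planning ICC of 0.05, and a nominal 95% Wald interval covers about 93%. The rate is about 8–9% only with all interactions in the model, and about 5% if schools hardly differ in change. The REML mixed model stays at 5.0% with t and about 5.8% with z.

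These figures assume school as a random effect, 40 schools, about 20 children per school and a two-sided test. A reader might infer that the trial's factor tests as a whole are invalid. The documents do not support that: the inflation is modest, is confined to the growth-curve branch, and would be avoided if the REML model carried the inference.

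**What to change.** Add one sentence to the analysis plan: the p-values and confidence intervals for the three factors at T2 and T3 come from the linear mixed model fitted by REML, with Kenward-Roger or Satterthwaite degrees of freedom (about 36 for the main-effects model). Use the growth curves to describe trajectories, or apply the same small-sample correction to their factor estimates before reporting p-values or intervals.

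No new data, schools or model are needed. The cost is main-effect intervals about 9% wider than the uncorrected maximum likelihood ones, and slightly lower nominal power.
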